### 2.5. Statistical Analyses

Statistical analyses will be performed using IBM/SPSS 26.0 (or a more recent version at the time of data analysis) (IBM Corporation, NY, USA) [70] and R Software (R Foundation for Statistical Computing, Vienna, Austria) [71]. For all statistical analyses, the significance level will be set to α = 0.05.

Two strategies for data analysis will be performed: intention-to-treat (ITT) and per-protocol (PP) analyses. ITT considers all participants allocated to arms at the baseline, thus providing a more conservative estimate of the treatment effect, allowing for noncompliance and protocol deviations. In this case, the last observation carried forward method will be used to deal with missing data. PP analysis includes the subset of participants who completed all evaluations. Results from both types of analyses will be reported when comparing control and intervention groups. For effect size estimation, only PP results will be used, since these allow the identification of the treatment effect under optimal conditions, i.e., without major deviations from the protocol. Sensitivity analyses will be carried out to identify potential effects of data strata and missing data on the outcome.

Univariate description of sociodemographic and outcome variables will be performed by providing central tendency (mean and median) and dispersion (standard deviation and range) measures for each moment of data collection. Normality tests (Kolmogorov–Smirnov test or Shapiro–Wilk test) in combination with kurtosis and symmetry analyses will be used to assess the distribution of the variables under study. Levene´s test will be used to assess homoscedasticity. Baseline between-groups comparisons, i.e., control versus intervention groups, will be tested through ANOVA or its non-parametric equivalent (Kruskal–Wallis) for continuous variables, and chi-square test for categorical variables. Mixed model repeated measure (MMRM) analyses will be used for the analyses of main and secondary outcomes, comparing between control and intervention groups and adjusting for relevant covariates (including potential confounding factors). Mediation and moderation analyses will be explored using structural equation modelling. Conceptually and statistically relevant variables will be selected to adjust the models. The size of the intervention effect will be assessed by calculating Cohen’s *d* coefficient [98] Cramer’s V, and odds ratio.

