Exclusion criteria at the baseline are: diagnosis of (a) a serious mental disorder (e.g., schizophrenia, schizoaffective disorder, other psychotic disorders, bipolar and related disorders, and personality disorders), (b) a chronic disease resulting in functional impairment, or (c) a neurodevelopmental disorder (e.g., autism spectrum disorders and intellectual disability); history of major depression; being under antidepressant medication; alcohol and/or drug addiction; high-risk pregnancy; and fetal malformations. These criteria were defined to ensure that relevant stress-related heterogeneity at the baseline will be reduced in the study. In addition to these exclusion criteria, mother–child dyads will be excluded from the study (after enrolment) in case of preterm birth (less than 37 weeks of gestational age), very-low weight at birth (less than 1500 g), or unexpected newborn malformations.

Randomization will follow the minimization procedure [67] aiming for a balanced sample size for educational level and age groups at the baseline (18–24 years old, 25–34 years old, and 35–40 years old). Random numbers and their assignment will be sealed in envelopes, kept in sequence and opened consecutively by trained researchers as pregnant women are screened for eligibility and enrolled in the study.

The minimum sample size for MAMH@WORK project will be 159, that is 53 women in each group. Attrition rate is considered to be approximately 40% and thus, a total of 225 pregnant women, 75 in each arm, will be enrolled in the study. These calculations are based on a literature review on psychological interventions for PPD prevention, which found mean depression scores (± standard deviation) of intervention and control groups of 11.00 ± 14.63 and 11.52 ± 14.93, respectively, at the final assessment of the study [39]. These sample size calculations assume the average difference between intervention and control arms reported by Dennis and Dowswell [39], considering a 95% confidence interval and a 80% power of the test to detect a difference between depression scores of both arms. This sample size allows for a medium effect size of the intervention to be detected for depression and anxiety scores.

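### All effect sizes come from women who completed every evaluation, and LOCF is the only missing-data method named for ITT; with about 40% attrition expected, neither is protected against bias

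*Protocol article*

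**What the plan says.** Section 2.5 plans two analyses and will report both when the arms are compared.

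- **ITT:** "ITT considers all participants allocated to arms at the baseline, thus providing a more conservative estimate of the treatment effect". For missing data, "the last observation carried forward method will be used to deal with missing data".
- **Per-protocol:** "PP analysis includes the subset of participants who completed all evaluations".
- **Effect sizes (Cohen's d, Cramer's V, odds ratio):** "For effect size estimation, only PP results will be used". The reason given is that this set shows the effect under optimal conditions, free of major protocol deviations.
- **Model:** "Mixed model repeated measure (MMRM) analyses will be used for the analyses of main and secondary outcomes". The text does not say whether the model is fitted to observed or to LOCF-filled data.
- **Sensitivity:** "Sensitivity analyses will be carried out to identify potential effects of data strata and missing data on the outcome". No method is named.

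Section 2.2 says "Attrition rate is considered to be approximately 40" per cent, with 225 women enrolled and a minimum of 159. Section 2.4 sets five data collection moments, from 28–30 weeks of gestation to twelve months postpartum.

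**The concern.** The set labelled per-protocol is a completers set. A woman who attends no session but completes all five assessments is in it; a woman who attends all 20 hours but misses one assessment is out. It therefore does not deliver the reason given for using it, yet every effect size comes from it. It is also selected on something that happens after randomisation. The trial is open-label with a care-as-usual control, so it cannot be presumed that women stay or leave for the same reasons in each arm.

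LOCF fits this schedule poorly. A woman lost between two weeks and five months postpartum has her two-week score entered as her twelve-month result. Three of the five sessions (3 × 4 = 12 of 20 hours) come in block 2, before return to work, so a two-week score will usually predate most of the intervention. For outcomes measured only after birth, a woman lost before her first such measurement has nothing to carry forward.

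At stake is whether the published effect sizes keep the randomised comparison, and whether the ITT result can serve as the cautious counterweight that the plan describes.

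**Working it through.** **1. How many women are involved.** From section 2.2:

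- At 40% attrition: 225 × 0.60 = 135 completers (45 per arm), with 225 − 135 = 90 women outside every effect size.
- If the minimum of 159 is met: 159 / 225 = 70.7% completers (53 per arm), a loss of 29.3%.

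**2. Whether LOCF can fill the ITT set.** Table 1 lists the PBQ, CARE-Index and Strange Situation under postpartum only. No earlier value exists for them, so LOCF cannot give a result for every allocated woman. The same holds for the EPDS if its postpartum entry is read literally. That is less certain, because the same row describes the EPDS as suitable for pregnant women and the schedule in Figure 1 is not shown.

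**3. How large the bias could be.** The documents give no dropout mechanism, so this is illustrative. Assumed inputs: 400,000 women per arm; three postpartum visits; control means 8.0, 7.0 and 6.5; SD 5; correlations 0.5–0.6; dropout possible after the first and second visits, 22.5% per step at the mean (1 − 0.775² = 40% in all); where dropout depends on the score, log-odds rise by 1 per SD of the last score (about 44% lost in that arm under no effect). The growing benefit is 0.5, 1 and 2 points. Results are control minus intervention at the last visit, in EPDS points, so positive favours the intervention.

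| True effect | Score-driven dropout in | Completers | LOCF |
|---|---|---|---|
| 0 | both arms alike | 0.0 | 0.0 |
| 0 | intervention only | +1.1 | −0.7 |
| 0 | intervention only, half the slope | +0.6 | −0.4 |
| 0 | control only | −1.1 | +0.7 |
| growing to 2.0 | neither arm | 2.0 | 1.5 |
| growing to 2.0 | both arms alike | 1.9 | 1.5 |
| growing to 2.0 | intervention only | 3.0 | 0.8 |
| growing to 2.0 | control only | 0.9 | 2.2 |
| constant 2.0 | neither arm | 2.0 | 2.0 |

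The completers figure of 3.0 becomes 3.1 if dropout is centred on the intervention arm's own mean. A bias of 1.13 points is 1.13 / 5 = 0.23 SD. Likelihood estimation on all observed data returned 0.0 and 2.0, as it must, because dropout depended only on scores already observed (missing at random).

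**4. A second set of assumptions, in SD units.** Correlation 0.5; time trend 0 or ±0.5 SD; dropout in control/intervention of 40/40, 30/50 or 50/30%; dropout unrelated to the score, related in both arms, or related in the intervention arm only.

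- True effect 0: completers −0.10 to +0.26, LOCF −0.25 to +0.13.
- True effect 0.5: completers 0.39 to 0.76, LOCF 0.07 to 0.52.

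The +0.13 for LOCF arose with 50/30% dropout and the same score dependence in both arms. It favours the intervention when nothing is there, so LOCF is not reliably conservative.

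**The case against.** The strongest reply has four parts.

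- **Both analyses are reported, an MMRM is named and missing-data sensitivity analyses are promised.** True, and it limits the point. But only the group comparisons come from both sets; effect sizes do not. An MMRM fitted to LOCF-filled data inherits the LOCF bias, and one fitted to observed data has no need of LOCF. An unnamed sensitivity analysis does not change where the reported effect size comes from.
- **The simulated bias depends on unsupported assumptions.** This stands. The documents do not say that score-driven dropout would occur in one arm only. With the same mechanism and rate in both arms the null bias vanishes; with the mechanism moved to the control arm the signs reverse; with a constant effect and dropout unrelated to score, LOCF is right. A reader might infer that both results will be biased, or that completers will overstate and LOCF understate the benefit. The documents do not support either reading.
- **Likelihood looks perfect only because dropout was simulated as missing at random.** Also correct. It would not be protected if dropout depended on unobserved mood.
- **An MMRM does not solve everything.** The Strange Situation gives four categories, to which a continuous-outcome MMRM does not apply. Odds ratios do not come from such a model. A woman with no postpartum value contributes no outcome to it. The fix has to allow for all three.

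**Conclusion.** The point holds as a lack of protection, not as a demonstrated bias. Three rules are written into section 2.5 and are not detail left to an analysis plan: effect sizes from completers only, a completers set labelled per-protocol, and LOCF for ITT. Together with the expected attrition they can give wrong answers.

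Two conclusions need no simulation. The completers definition does not match its stated reason, and LOCF cannot produce an all-allocated set for the PBQ, CARE-Index or Strange Situation if any woman is lost before her first value.

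The size rests on the assumptions above. With no true effect it spans −1.1 to +1.1 EPDS points for completers and −0.7 to +0.7 for LOCF, through about 0. With a benefit growing to 2.0 points it spans 0.9 to 3.0 and 0.8 to 2.2. The direction cannot be predicted from the documents. The change should be made before analysis, because it is cheap and the effect sizes are what readers will carry away.

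**What to change.** In section 2.5:

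1. Delete LOCF.
2. For repeated continuous outcomes, make the MMRM on all observed data, by randomised allocation, the main analysis. Take the effect size from it as a standardised difference with a 95% confidence interval.
3. For categorical or single-visit outcomes, use a matching model (for example logistic) on all allocated women, with multiple imputation from baseline data where no postpartum value exists.
4. Rename the present per-protocol set as completers and report its effect sizes as supplementary only. Base any true per-protocol set on session attendance.
5. Direct the missing-data sensitivity analysis already promised at departures from missing at random. Delta-adjusted imputation is one option; the choice can rest with the analysis plan.
6. Remove the statement that the ITT estimate is more conservative.

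The cost is a change of wording and modest programming. Effect sizes may turn out less favourable than those from completers.

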Strategies to reduce attrition during the experimental period will be implemented. At recruitment, pregnant women will be provided with detailed information about the project, including the objectives and participant’s role in the study. During post-allocation period, referrals to other healthcare professionals will be performed as necessary, and the required logistic support for data collection will be provided, such as scheduling suitable data collection appointments [69]. Reminders will be sent to enrolled women one week before the scheduled date of each data collection moment. Women in the intervention group with biomonitoring of physiological signals will receive tailored health-related information based on data collected through wearable devices (biofeedback), whereas women in both the control and intervention arms will receive general health information via a smartphone app (also accessible in the private area of the project’s website). This app will be developed specifically for MAMH@WORK project and will be available for download by all women enrolled in the study. It will mirror information available at the website and facilitate communication between the research team and participants. 

The main outcomes that will be used to assess the effectiveness of the intervention are women’s psychological wellbeing (mood disorders and anxiety disorders, assessed by the Hospital Anxiety and Depression Scale/HADS and by the Edinburgh Postnatal Depression Scale/EPDS), subjective wellbeing (Self-Report of Happiness), quality of mother–child interactions (assessed by the CARE-Index) and child-mother attachment (assessed by the Strange Situation Procedure and by the Postpartum Bonding Questionnaire/PBQ). Secondary outcomes include child emotional self-regulation and cognitive self-control; women’s job engagement and presenteeism; and women’s physiological signals (pulse rate, pulse rate variability, and sleep patterns).

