**Child-mother Attachment, Child Emotional Self-regulation and Cognitive Self-control**		
The Strange Situation Procedure	This task involves a sequence of eight 3-min episodes designed to place moderate although increasing levels of stress on infants (i.e., unfamiliar play room, interacting with a stranger, and two separations from the mother). Videotapes of infants’ attachment behavior during the Strange Situation Procedure will be scored by trained, reliable coders following the procedures developed by Ainsworth and colleagues [86]. Infants will be classified as either securely attached (B), insecure–avoidant (A), insecure–ambivalent (C), or disorganized–disoriented (D).	Postpartum
Postpartum Bonding Questionnaire (PBQ) [87]	PBQ is a screening tool for mother-child bonding impairment. Women are asked to rate how often they agree with several statements on their feelings or attitudes towards their child. It is composed of four subscales: impaired bonding, rejection and anger, anxiety about care, and risk of abuse. High scores indicate impaired bonding. Instrument validated for the Portuguese population [88].	Postpartum
Questionnaire on the Difference Imaginary Baby vs. Real Baby (QDIBRB) [89]	QDIBRB-30 screens for differences between mother’s prenatal and postnatal perceptions in three dimensions: child positive emotional expressions, mother’s fears about behavioral meaning, and child appealing behavior. Respondents indicate their agreement with each statement in a 5-point Likert scale ranging from completely disagree to completely agree. High scores indicate large differences between imaginary and real baby. Developed, tested and validated for Portuguese women.	Postpartum
Schedule of Growing Skills II (SGS-II) [90]	SGS-II is a screening tool for psychomotor development that considers nine areas: passive posture, active posture, locomotion, manipulation, visual, hearing and language, speech and language, interactive social, self-care social and cognition. Children are classified as having an adequate or delayed development. Instrument validated for the Portuguese population [91].	Postpartum
Toy Removal Task [92]	2-min toy removal episode preceded by 90 s of playing between mother and child. During removal and after returning the toy, mothers will be instructed to stay non-interactive and assume a neutral expression.	Postpartum

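### Section 2.5 applies MMRM to every main outcome, but the Strange Situation Procedure gives one of four unordered classes, so no interpretable intention-to-treat analysis is stated for it

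*Protocol article*

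**What the plan says.** Section 2.5 (Statistical Analyses) of the protocol article names one model for the effectiveness outcomes: "Mixed model repeated measure (MMRM) analyses will be used for the analyses of main and secondary outcomes". The sentence goes on to cover the comparison of control and intervention groups and covariate adjustment. It makes no distinction by type of outcome.

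Section 2.4 lists among the main outcomes "child-mother attachment (assessed by the Strange Situation Procedure and by the Postpartum Bonding Questionnaire/PBQ". Table 1 describes how the first of these is scored: "Infants will be classified as either securely attached (B), insecure–avoidant (A), insecure–ambivalent (C), or disorganized–disoriented (D". It describes no continuous score for this procedure.

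Table 1 also describes the SGS-II, a developmental screening tool, as two-valued: "Children are classified as having an adequate or delayed development". Section 2.4 does not name the SGS-II in its outcome lists. It does say "Secondary outcomes include child emotional self-regulation and cognitive self-control", and the SGS-II falls in that domain by its Table 1 heading and by the abstract.

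Elsewhere in Section 2.5, the effect-size measures are Cohen's d, "Cramer’s V, and odds ratio". The section also says "For effect size estimation, only PP results will be used". The one categorical test named, "chi-square test for categorical variables", belongs to the sentence on baseline comparisons between groups.

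**The concern.** MMRM in its ordinary sense is a linear model for a continuous response measured repeatedly. An attachment class is a name, not a quantity: avoidant, secure, ambivalent and disorganised have no agreed order and no distances between them. To enter the label into such a model, someone must number the classes, and the estimate, its sign and its p-value then follow from that numbering.

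Attachment is one of the trial's stated aims, and the Strange Situation is its observational measure. Followed literally, Section 2.5 gives a result for it that cannot be interpreted. If it is not followed, the model and any grouping of the four classes are open to choice after the data are seen.

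**Working it through.** **1. Outcome type against stated model.**

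| Item | Source | Content |
|---|---|---|
| Model for outcomes | Section 2.5 | MMRM, main and secondary, no exception |
| Strange Situation, status | Section 2.4 | main outcome |
| Strange Situation, scale | Table 1 | four unordered classes |
| Chi-square test | Section 2.5 | baseline comparisons only |
| Odds ratio, Cramer's V | Section 2.5 | effect sizes, per-protocol only |
| Structural equation modelling | Section 2.5 | mediation and moderation only |

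No logistic, multinomial or generalised mixed model is named for any outcome. The plan gives no figure to reproduce on this point.

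**2. How far the numbering matters.** The group size of 53 per arm is the minimum in Section 2.2. The class shares are assumed: A/B/C/D of 15/55/10/20% in control and 10/70/10/10% in one intervention arm. Rounded to 53, the counts are control 8/29/5/11 and intervention 5/38/5/5. The test is a two-sample t test, t = (difference in mean code) / (s_p × √(2/53)), on 104 df.

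- Numbering A=3, B=1, C=2, D=4:
  - Control mean = (24 + 29 + 10 + 44)/53 = 107/53 = 2.019.
  - Intervention mean = (15 + 38 + 10 + 20)/53 = 83/53 = 1.566.
  - Difference = −24/53 = −0.453.
  - Variances: (297 − 107²/53)/52 = 1.557 and (183 − 83²/53)/52 = 1.020, so s_p = √((1.557 + 1.020)/2) = 1.135.
  - t = −0.453/(1.135 × 0.1943) = −2.05, p = 0.043.
- Numbering A=4, B=2, C=3, D=1:
  - Control mean = (32 + 58 + 15 + 11)/53 = 116/53.
  - Intervention mean = (20 + 76 + 15 + 5)/53 = 116/53.
  - Difference = 0, p = 1.00.
- All 24 numberings: p runs from 0.043 to 1.00. The difference is positive in 11, negative in 11 and zero in 2. The even split of signs is expected, because reversing any numbering reverses the sign. The spread of p comes from the data being identical and only the labels changing.

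**3. Analyses of the same counts that do not depend on numbering.** The 4 × 2 chi-square is 4.15 on 3 df, p = 0.25. For secure against not secure, the split is 38/15 in intervention and 29/24 in control, so the odds ratio = (38 × 24)/(15 × 29) = 912/435 = 2.10. Both keep their value whatever numbers are attached to the classes.

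**4. SGS-II.** With two classes coded 0/1, a linear comparison estimates a risk difference. In 20,000 simulated trials at 53 per arm under no effect, its type I error was 0.045, 0.047 and 0.048 at assumed rates of 5, 10 and 20%. The mismatch does not invalidate the test there.

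**The case against.** The strongest reply is that nobody intends to number the classes. Section 2.5 proposes no coding. It lists the odds ratio and Cramer's V, which a linear model does not produce, so some categorical analysis is foreseen. The text is a condensed journal article, and the model for each outcome type is commonly left to the analysis plan.

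Part of this stands: the likely cause is a compressed sentence. But the article is not silent. It assigns a model to all main and secondary outcomes, and for this one the model does not fit. An analysis plan that follows the sentence inherits the mismatch; one that departs from it contradicts the published text. The odds ratio and Cramer's V do not close the gap, since they are effect sizes for the per-protocol set.

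It is also fair to say that the PBQ, the second attachment instrument, is a scored questionnaire and is not affected.

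A reader might infer four stronger things that the documents do not support.

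- *That the analysis is invalid for the SGS-II too.* The simulation above shows otherwise, and Section 2.4 does not name it as an outcome.
- *That the Strange Situation is measured once, so that nothing can be carried forward.* Table 1 gives its timing only as postpartum, Section 2.4 has three postpartum visits, and Figure 1 is not shown.
- *That the trial loses a known amount of power.* With assumed shares of 20/60/10/10% against 10/80/5/5% and codes 1 to 4, the linear comparison has about 6% power and secure versus not secure about 62%. A second assumed split (15/60/10/15% against 7.5/80/5/7.5%) gives about 13% and 63%. These figures reflect the chosen shares and coding and are not a property of this trial.
- *That Cramer's V must be dropped.* It has no sign, but beside an odds ratio it does no harm.

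**Conclusion.** The point holds for the Strange Situation Procedure. The stated model does not suit a four-class unordered label, and no other statement in Section 2.5 supplies an ITT analysis for it. This rests on reading MMRM in its usual linear sense and on Table 1 describing the only scoring to be used. It does not depend on whether the procedure is repeated.

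Its size cannot be given as a bias or power figure for this trial. The range of p from 0.043 to 1.00 belongs to one assumed data set and shows only that the answer is arbitrary. The problem concerns one of two instruments for one main outcome. For the SGS-II, a logistic model would match better, but that is a refinement. The correction should be made before analysis, since it concerns a main outcome and costs little.

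**What to change.** In Section 2.5, or in the analysis plan with a note that it refines Section 2.5:

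- Restrict MMRM to continuous scores measured repeatedly.
- Name in advance a categorical model for the Strange Situation in the ITT set. One suitable choice is logistic regression of secure (B) versus not secure (A, C, D), adjusted for the minimisation factors (age group and educational level). Report the odds ratio with 95% CI and show the four-class table as descriptive. A multinomial model is an acceptable alternative.
- If the procedure is assessed more than once, use a repeated-measures version (GEE or a generalised mixed model).
- Preferably, analyse the SGS-II classification by logistic regression as well.

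The cost is a few sentences and no new data. If the classes are collapsed, some detail on the insecure subtypes is lost from the model and remains only in the descriptive table.
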